### Secondary Outcomes

#### Mini-Mental State Examination (MMSE)

The Mini-Mental State Examination (MMSE) is a validated scale to assess cognitive performance in both research and clinical settings [36]. It contains 20 items and scores range from 0-30, with a higher score denoting better cognitive function. The Chinese version of the MMSE has good psychometric properties, with satisfactory internal consistency (Cronbach’s alpha=.86) and test-retest reliability (alpha=.78), and good inter-rater reliability (ICC=.99) [37].

#### Cornell Scale for Depression in Dementia (CSDD)

The Cornell Scale for Depression in Dementia (CSDD) is a validated scale used to assess the signs and symptoms of major depression in patients with dementia [44]. The information is elicited through two semi-structured interviews, one with the patient and one with the caregiver. The scale is divided into the following five sub-scales (1) mood-related signs, (2) behavioural disturbance, (3) physical signs, (4) cyclic functions, and (5) ideational disturbance. There are 19 items, of which each can be given a score ranging from 0 (absent) to 2 (severe). The total score ranges from 0-38; a higher score denotes greater levels of depression. The Chinese version of the CSDD demonstrated satisfactory internal consistency (Cronbach’s alpha=.84) and inter-rater reliability (kappa=.43-.89) [45,46].

#### Zarit Burden Inventory (ZBI)

The Zarit Burden Inventory (ZBI) is a validated scale to assess caregiver burden [47]. It contains 22 items, each of which can be given a score ranging from 0 (never) to 4 (nearly always). The total score ranges from 0-88; a higher score denotes greater perceived caregiver burden. The Chinese version of the ZBI showed a good internal consistency reliability (ICC=.99, split half correlation coefficient=.81) [48].

### Other Assessments

#### Subjective Impression Questionnaire

Subjective impression of PARO will be assessed at the end of each session of the PARO therapy by adopting four items from studies conducted by Shibata et al [29,49], with two of them reflecting subjects’ preference towards PARO and the other two for understanding their own feelings when interacting with PARO and their readiness to receive the PARO therapy. The four questions are (1) Is PARO cute/ugly?, (2) Do you like/dislike PARO?, (3) Is playing with PARO fun or boring?, and (4) Do you want to play with PARO again? For the group assigned to the psychosocial activities, four similar questions will be used (1) Is the activity interesting/not interesting?, (2) Do you like/dislike the activity, (3) Is the activity fun or boring?, and (4) Do you want to join the activity again?

#### Qualitative Comments

Qualitative comments from the caregivers, the facilitator, and the therapists will also be obtained from semi-structured qualitative interviews. Interviews will be conducted within one month of completing the treatment program. For the caregivers, the interviews will explore their perceptions of the impact of dementia on the subjects’ daily lives, experiences of the interventions that were designed to improve mood and encourage social interaction and communication since diagnosis, and feedbacks after the treatments. For the facilitator and the therapists, the interviews will elicit information about the subjects’ reactions towards each treatment. Furthermore, the challenges of subject recruitment, treatment implementation, as well as the factors associated with interest in engagement and adherence of the treatments will also be obtained.

### Piloting

Prior to the study, a pilot study was performed to explore the feasibility and potential benefits of PARO therapy in older adults with dementia. Using a pre-post single group design, community-dwelling older Chinese adults with mild cognitive impairment or mild to moderate dementia were recruited to receive six sessions of the PARO therapy (one 30-minute session per week for six consecutive weeks) in Shatin Hospital. The PARO therapy was delivered in a structured, small-group approach, in which a group of 3-4 subjects were arranged to sit around a table with PARO in the centre. An occupational therapist familiar with the PARO caregiver’s manual delivered the PARO therapy (Figure 3). The mean age of the 7 subjects that completed the PARO therapy was 78.6 (range 72-87, SD 5.3), of which 43% (3/7) were female, and with a mean MMSE score of 19.3 (range 16-22, SD 2.8). Using the Wilcoxon signed ranks test, there was a significant improvement in mood, as evaluated by the simplified face scale, following the PARO therapy (*P*=.02). Social interaction and communication was evaluated by video analysis of facial expressions and reactions towards PARO using a time sampling method where the 30 minutes of video were divided into 30 units, and each one minute unit was checked for the occurrence of each facial expression and reactions towards PARO. The analysis showed that the frequency of neutral expressions during the six 30-minute sessions was high (mean observed frequency of the six sessions was 27 minutes out of 30 minutes), followed by smile (13 minutes out of 30 minutes), and laugh (9 minutes out of 30 minutes). Furthermore, all subjects gently stroked or held PARO during the interaction, and talked directly with PARO in a dyadic relation as if it was a real living pet. In addition, there was a positive trend in depressive symptoms, as evaluated by CSDD (*P*=.03) and a falling trend in caregiver burden, as evaluated by ZBI (*P*=.02) immediately following the PARO therapy. All subjects completed the six-session PARO therapy, with the attendance rate of 100%. Thus, our findings provide important preliminary support for the use of social robot in engaging older patients with dementia in a day care setting. The questionnaires and assessment protocols have been pilot-tested.

**Figure 3 figure3:**
[figure not shown]
PARO therapy.

### Sample Size Calculation

Sample size calculations were based on the effects on mood in the pilot study: a sample size of 15 subjects per group will allow us to detect differences among the mean values of face scale scores (0.63, SD 0.74) between pre- and post-interventions using one sample *t* test (alpha=.05 and power=.9). Given that the attrition rate of 20% was observed in a previous PARO study of people with dementia [30], we will estimate a more conservative attrition rate of 25%, and thus we will recruit a total of 40 subjects.

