To date, the potential benefits of PARO therapy in Hong Kong Chinese have not been systematically examined. Given the successful application of PARO therapy, and the encouraging findings of its positive effects on mood and social interaction and communication, it is suggested that PARO therapy is both feasible and acceptable to elderly people with dementia. Therefore, in this study protocol, we describe the design of a RCT aiming to confirm the findings of our pilot data (see Piloting in the Method section), by providing an evaluation of the effectiveness and benefits of the use of PARO in dementia care in Hong Kong.

The primary objective of the present study is to examine whether robot-assisted intervention using PARO in older Chinese adults with mild to moderate dementia improves mood, and stimulates social interaction and communication compared to psychosocial activities by conducting a methodologically rigorous RCT. Secondary objectives are to examine the effects of PARO therapy on cognitive function, depressive symptoms, and caregiver burden compared to those of psychosocial activities.

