### Statistical Analysis

Double data entry, consistency check, and data cleaning will be performed prior to data analysis. An intention-to-treat (ITT) analysis will be carried out, in that all available data will be included, without considering the subjects’ compliance to the allocated treatment. Mean and standard deviation will be used for continuous variables while frequency and percentage will be used to describe the distribution of ordinal and categorical variables. Unpaired tests will be used for the primary analysis. Differences between the intervention and control groups in relation to outcome measures will be compared using an analysis of variance (ANOVA) or independent *t* tests. In order to increase precision in estimating the effect of interest, the analysis of covariance (ANCOVA) will be used to take into account the possible confounding effects of the covariates, such as age, education, etc. A mixed-model, repeated-measures ANCOVA will be used to compare the reactions towards each treatment captured by the observation table in both groups. The effect size will be computed to show the magnitude and direction of the effect of the intervention group relative to the control condition for each outcome variable. Data analyses will be conducted by SPSS Statistics software. A *P*<.05 will be taken as the level of statistical significance. The 95% confidence interval around the differences will be calculated.

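### The 90% power belongs to a one-sample pre-post test, not to the planned between-arm comparison, for which 15 per arm gives about 61% under the plan's own inputs

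*Protocol article*

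**What the plan says.** Under Sample Size Calculation, the protocol article says that "a sample size of 15 subjects per group will allow us to detect differences". The target is to "detect differences among the mean values of face scale scores (0.63, SD 0.74") and the test is named as one "between pre- and post-interventions using one sample *t* test (alpha=.05 and power=.9"). With 25% attrition this becomes 40 recruited. The section attributes the effect to the pilot, which the Piloting section describes as "Using a pre-post single group design", with no control group.

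The question is set elsewhere. The primary objective in the Introduction is improvement "compared to psychosocial activities by conducting a methodologically rigorous RCT". Under Statistical Analysis, "Unpaired tests will be used for the primary analysis", and differences between the arms are to be tested by ANOVA or independent t tests. The Control Group section describes an active comparator: facilitated table games in groups of three to four, on the same schedule and with the same facilitator. The article gives no expected change in controls and no expected between-arm difference.

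**The concern.** A one-sample test on change asks whether one group moves from its own starting point. An unpaired test asks whether two groups move by different amounts. For the same mean and SD, the second needs about twice as many subjects in each arm, because the control mean must be estimated too. Using the within-group change as the target also credits PARO with all of the pilot improvement, including whatever came from attention, company, repeat testing or time. An active control may share those elements.

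At stake is the only power statement in the article, made for a primary outcome. A reader who takes 90% at face value would treat a non-significant mood result as a well-powered negative. Under the plan's own figures the design would miss the assumed effect about four times in ten, and more often if controls improve.

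**Working it through.** **Inputs.** Mean change 0.63, SD 0.74, alpha .05, power .9, 15 per group, 25% attrition (Sample Size Calculation). Between-arm unpaired test (Statistical Analysis). Assumed because the article does not state them: two-sided testing, equal allocation, SD 0.74 for change in both arms, independent subjects.

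**1. Reproduce the plan's figure.** Standardised effect d = 0.63/0.74 = 0.851. One-sample normal formula: n = (1.960 + 1.2816)² / 0.851² = 14.5, rounded up to 15. Attrition: 2 × 15 / 0.75 = 40. Both figures reproduce. The one-sided version gives 11.8, so 15 points to a two-sided calculation.

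**2. Power of the planned comparison, controls unchanged.** Noncentrality λ = d × √(n/2), with 2n − 2 degrees of freedom; power is the probability that the noncentral t exceeds the critical value in absolute size.

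- n = 15 per arm: λ = 0.851 × √7.5 = 2.33, 28 df, critical value 2.048; power 61% (64% by normal approximation).
- n = 20 per arm, no attrition: λ = 0.851 × √10 = 2.69, 38 df, critical value 2.024; power 75%.
- For 90%: the normal formula gives 2 × 14.5 = 29 per arm. The exact t test needs 30, so 60 evaluable and 60/0.75 = 80 recruited.
- Difference detectable with 90% power at 15 per arm: d = 1.226, or 1.226 × 0.74 = 0.91 points.

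**3. If controls also improve (assumed values, 15 per arm).**

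| Control change, share of 0.63 | Net difference | Power |
|---|---|---|
| 0% | 0.63 | 61% |
| 25% | 0.47 | 39% |
| 50% | 0.315 | 20% |

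**4. Other variants, one at a time, 15 per arm, controls unchanged.**

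- One-sided t test: 74%.
- Covariate adjustment, replacing d by d/√(1 − r²): 66% at r = 0.3, 74% at r = 0.5, 88% at r = 0.7 (r is the assumed correlation of covariates with outcome).
- Post-treatment scores alone, with an assumed pre-post correlation of zero: the SD becomes 0.74/√2 = 0.523 and power is 89%.
- Correlation within therapy groups averaging 3.5 members, design effect 1 + 2.5 × ICC: an assumed ICC of 0.05 gives 1.125 and about 56% power.

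None reaches 90%. The two that come close rest on extreme assumptions.

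**The case against.** The best defence is that 61% is not a ceiling, and that is right. A reader might infer that the trial has at most 61% power, but the documents do not support a bound. The figure is for 15 analysed per arm, a two-sided unadjusted test, SD 0.74 in both arms and controls who neither improve nor worsen. The analysis is intention-to-treat on all available data, so more than 15 per arm may be analysed. ANCOVA is planned for precision. The face scale is taken before and after each of six sessions, so averaging could change the SD. Stacking favourable assumptions can pass 90%: 20 per arm with no loss and r = 0.7 gives d/√(1 − 0.49) = 1.19 and 96% power. But the article itself allows for 25% attrition, gives no covariate correlation, and builds none of this into its sample size. The figure is conditional; the mismatch stands.

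Four other stronger readings also go too far:

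- *The sample size is an arithmetic error.* It is not; 15 and 40 both reproduce.
- *The calculation fails even for its own test.* A two-sided one-sample t test has 86.5% power at n = 15 and needs 17 for 90%, but a one-sided one has 93% at 15. Sidedness is not stated (the article says only "A *P*<.05 will be taken as the level of statistical significance"), and rounding up a normal-formula answer is common. This is secondary.
- *The pilot effect is compatible with zero.* With the seven completers, 0.63 ± 2.447 × 0.74/√7 runs from −0.05 to 1.31. But the article does not say that seven subjects supplied these figures. Whole-point changes in eight would fit better (5/8 = 0.625; changes of 0,0,0,0,1,1,1,2 have SD 0.744), and n = 8 gives 0.01 to 1.25. The Piloting section also reports a Wilcoxon P of .02 for mood. The interval should not be used.
- *The trial cannot confirm the pilot.* The pilot finding was a within-group change, which the one-sample calculation does address. What lacks the stated power is the comparison with control.

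It is also fair to say that the Statistical Analysis section already plans effect sizes relative to control and 95% confidence intervals for the differences, so part of the remedy is in place.

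**Conclusion.** The concern holds as a mismatch between sizing and analysis. The stated power of 0.9 describes a test that is not the primary analysis. For the planned unpaired comparison, on the article's own inputs, power is about 61%, roughly 30 percentage points below the claim. It would be about 75% if all 40 recruited subjects were analysed.

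These figures rest on the assumptions listed with the calculation. The one the documents give least reason to accept is that an active control produces no mean change in mood; relaxing it cuts power quickly. Adjustment or a one-sided test would raise power and correlation within therapy groups would lower it. No single plausible variant brings 15 evaluable per arm to 90%.

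**What to change.** Keep the recruitment target of 40. In Sample Size Calculation, delete the one-sample basis and replace it with a statement such as:

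> Fifteen evaluable subjects per group give about 61% power (two-sample t test, two-sided alpha .05, unadjusted) for a between-group difference in face-scale change of 0.63 with SD 0.74 in both groups, assuming no mean change in controls and no correlation within therapy groups. Power is lower if controls improve. Power of 90% is available for a difference of about 0.91 points.

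This wording takes face-scale change as the endpoint. The Statistical Analysis section refers only to outcome measures, so the team should confirm that change is what will be compared. Add a sentence there saying that the mood result will be interpreted through the between-group estimate and its already planned 95% confidence interval, and that a non-significant result will not be read as evidence of no effect.

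The cost is wording only. No subjects, visits or analyses are added; the price is a less favourable power statement.

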### Statistical Analysis

Double data entry, consistency check, and data cleaning will be performed prior to data analysis. An intention-to-treat (ITT) analysis will be carried out, in that all available data will be included, without considering the subjects’ compliance to the allocated treatment. Mean and standard deviation will be used for continuous variables while frequency and percentage will be used to describe the distribution of ordinal and categorical variables. Unpaired tests will be used for the primary analysis. Differences between the intervention and control groups in relation to outcome measures will be compared using an analysis of variance (ANOVA) or independent *t* tests. In order to increase precision in estimating the effect of interest, the analysis of covariance (ANCOVA) will be used to take into account the possible confounding effects of the covariates, such as age, education, etc. A mixed-model, repeated-measures ANCOVA will be used to compare the reactions towards each treatment captured by the observation table in both groups. The effect size will be computed to show the magnitude and direction of the effect of the intervention group relative to the control condition for each outcome variable. Data analyses will be conducted by SPSS Statistics software. A *P*<.05 will be taken as the level of statistical significance. The 95% confidence interval around the differences will be calculated.

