### Intervention Group

The PARO therapy will take place for 30 minutes once a week over a six week period, and will be delivered in a quiet room that is isolated from the common unit (ward) in the Occupational Therapy Department of Shatin Hospital, with minimal environmental distractions. The number of sessions, the length of each session, and the time frame of this study were decided based on the results of our pilot study (see Piloting of this section) and other PARO intervention studies which reported small or significant changes in mood, social interaction, and communication [15]. Given this, one 30-minute session per week for six consecutive weeks would allow sufficient time for identifying significant changes, and would also reduce the burden of commitment for subjects.

The PARO therapy will be delivered in a structured, small-group approach, in which a group of three to four subjects will be arranged to sit around a table with PARO in the centre. The subjects in each group can be substituted by subjects from other groups to optimize the chance of conducting each session. A facilitator who is familiar with the PARO caregiver’s manual will deliver the PARO therapy. Research team therapists will train the facilitator and monitor the sessions.

The PARO therapy is based upon a standardised framework, and involves activities around the concepts of engaging, social interaction, and communication. There are six stages/themes, including (1) introducing PARO, (2) baby-sitting PARO, (3) grooming PARO, (4) feeding PARO, (5) making over PARO, and (6) wardrobe PARO. During each session, the facilitator will show PARO to each subject and demonstrate how PARO responds. Subjects will be encouraged to touch and hold PARO, describe the features and appearance of PARO, and help take care of PARO. The session will proceed for at least 30 minutes. With one session per week, there will be at least a total of 180 minutes of the treatment in the six week period.

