### Control Group

Subjects assigned to the control group will be invited to practise a variety of psychosocial activities including a range of table games (eg, Chinese checkers, Jenga, board games etc). The activities will be held on exactly the same schedule as the intervention group (one 30-minute session per week for six weeks). All activities will be carried out in groups of three to four subjects, and will be facilitated by the same facilitator of the intervention group. The sessions will proceed for at least 30 minutes. With one session per week, there will be at least a total of 180 minutes of the treatment in the six week period.

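### Both arms are treated at tables of three to four, but the fixed primary test assumes independent subjects; if scores correlate within tables, standard errors are too small

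*Protocol article*

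**What the plan says.** All places are in the Methods of the protocol article.

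- **Baseline Assessment and Randomization:** allocation is by individual, in blocks of six, stratified by gender.
- **Intervention Group:** PARO is given in small groups, "in which a group of three to four subjects will be arranged to sit around a table with PARO in the centre". Membership is not fixed: "The subjects in each group can be substituted by subjects from other groups to optimize the chance of conducting each session".
- **Control Group:** the same structure applies. "All activities will be carried out in groups of three to four subjects".
- **Observation Table:** this primary measure scores expression, gaze and interaction, including interaction with the other subjects at the table.
- **Statistical Analysis:** the primary analysis is by unpaired tests. The arms "will be compared using an analysis of variance (ANOVA) or independent *t* tests", with ANCOVA for covariates such as age and education. The observation table gets a mixed-model repeated-measures ANCOVA. "A *P*<.05 will be taken as the level of statistical significance".
- **Sample Size Calculation:** "a sample size of 15 subjects per group", with no allowance for treatment in groups.

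Clustering by table is not mentioned anywhere. Attendance at each session is to be recorded (Outcome Measures), but nothing says that the table attended will be.

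**The concern.** People at one table share a robot or a game, and they share each other's company. When one subject talks to or smiles at a neighbour, that is part of the neighbour's social setting. The Discussion itself prefers a group setting as the way to stimulate social interaction, so influence between subjects is part of the intended mechanism. Some positive correlation between scores at a table is therefore the natural expectation for the face scale and the observation table.

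An independent t test, or an ANOVA offered as its alternative, takes the standard error from the spread between subjects as if each were a separate unit. With positive correlation at a table, that standard error is too small, the confidence interval too narrow and the P value too low. Fifteen evaluable subjects make only four or five tables per arm, so one lively table can move an arm mean noticeably. A repeated-measures model deals with correlation within a subject over sessions, which is a different matter.

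**Working it through.** **Inputs from the article.** Tables of 3–4 in both arms; 15 evaluable subjects per arm; 25% attrition; mean change 0.63, SD 0.74; alpha 0.05; power 0.90. **Input not in the documents.** The within-table ICC. The range 0.01 to 0.30 is an assumption.

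**Step 1: the plan's own sample size.** It rests on "differences among the mean values of face scale scores (0.63, SD 0.74) between pre- and post-interventions", "using one sample *t* test (alpha=.05 and power=.9". With the normal approximation, two-sided:

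n = ((1.960 + 1.282) × 0.74 / 0.63)² = 14.50, rounded up to 15.

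15 / 0.75 = 20 per arm, 40 in total. The stated figures reproduce, and no design effect is in them.

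**Step 2: design effect and approximate error.** For tables of size m:

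DE = 1 + (m − 1) × ICC; the naive standard error is too small by a factor √DE; the actual two-sided error is about 2 × (1 − Φ(1.960 / √DE)).

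Example, m = 4 and ICC = 0.10: DE = 1 + 3 × 0.10 = 1.30; √1.30 = 1.140; 1.960 / 1.140 = 1.719; error = 8.6%.

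**Step 3: simulation.** The independent t test was run on 100,000 null trials per setting, 15 per arm, with table effects in both arms and fixed tables.

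| Assumed ICC | DE, m = 3 to 4 | √DE | Type I error, tables 3,3,3,3,3 | Type I error, tables 4,4,4,3 |
|---|---|---|---|---|
| 0 | 1.00 | 1.00 | 5.0% | 5.0% |
| 0.01 | 1.02–1.03 | 1.01–1.02 | 5.1% | 5.3% |
| 0.05 | 1.10–1.15 | 1.05–1.07 | 6.3% | 6.7% |
| 0.10 | 1.20–1.30 | 1.10–1.14 | 7.4% | 8.3% |
| 0.20 | 1.40–1.60 | 1.18–1.26 | 10.0% | 12.2% |
| 0.30 | 1.60–1.90 | 1.26–1.38 | 12.5% | 15.5% |

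**Step 4: information lost.** At an average of 3.5 per table, DE is 1.025, 1.125, 1.25, 1.50 and 1.75 for ICC 0.01 to 0.30. Thirty evaluable subjects then carry the information of 30 / DE = 29, 27, 24, 20 and 17 independent ones.

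**Step 5: effect of substitution.** This illustration analyses the mean of six sessions, with 20 per arm at five tables of 4 and a between-subject variance share of 0.3. If tables are fully reshuffled every week, type I error is 5.6%, 6.3% and 7.5% at session-level ICC 0.05, 0.10 and 0.20. If tables stay fixed and their effect persists, it is 9.2%, 12.3% and 17.6%. These fixed-table figures exceed those in the table because averaging shrinks the session noise but not a persistent table effect. At session ICC 0.05, the ICC of the six-session mean is 0.05 / (0.05 + 0.30 + 0.65/6) = 0.11. Mixing reduces the excess and does not remove it.

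**Step 6: which random effects are needed.** A mixed model with intercepts for subject and table-session only was simulated with 4 tables of 4 per arm, six sessions and 1,500 null trials per setting. With a persistent table variance of 0.05, 0.10, 0.20 or 0.30, its type I error was 6.5%, 8.9%, 12.8% or 15.2%, against 7.3%, 9.5%, 13.4% or 16.0% for the naive t test. Without a persistent table term, most of the inflation stays. When table effects did not persist from week to week, the same model gave 5.5%.

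**The case against.** **The most social outcome is not assigned the t test.** The observation table gets a mixed model, and a condensed article may leave its random effects to the analysis plan. This stands in part: a table term could still be specified there. But the article describes the model only as repeated-measures, and the face scale, also primary, is left to the unpaired test, which has no place for a table effect.

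**The ICC is unknown, so the inflation is assumed.** This stands. A reader might infer that type I error necessarily exceeds 5%; the documents do not support that. At ICC 0.01 the excess is negligible. Correlation may be weak for MMSE, CSDD and ZBI, the last of which measures the caregiver's burden. It could even be negative for items on which subjects compete for one PARO.

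**Tables need not be fixed.** This stands as to size: substitution is permitted, not required, and the more it mixes tables, the smaller the excess.

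Two other inferences are tempting and fail. The shared facilitator might seem to be a source of the inflation, but the Control Group section gives both arms the same facilitator, so this does not separate the arms. The substitution rule might be read as allowing exchange between arms. It stands in the Intervention Group section, directly after the PARO tables are described, and the Control Group section has no such rule, so that reading is strained.

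**Conclusion.** The point holds in conditional form. The protocol fixes a primary test that assumes independent subjects, for treatments delivered to interacting groups of three to four. This is a stated method that does not fit the stated delivery, not a detail left for later. If within-table correlation is positive, standard errors are too small by a factor of about 1.01 to 1.38 over the assumed ICC range of 0.01 to 0.30. With 15 per arm at fixed tables, the nominal 5% test then rejects a true null in about 5% to 16% of trials. The excess is slight at 0.01, becomes material from about 0.05 to 0.10, and is smaller where substitution mixes the tables. The conclusion is firm for the mismatch between design and test. Its size is an assumption, and it bears mainly on the face scale and the observation table.

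**What to change.** 1. **Record the table.** Add to the attendance log the assigned table and the table actually attended at each session. This must be done during the trial, because the analysis cannot allow for substitution without it.
2. **Face scale and observation table.** Replace the unpaired test by a linear mixed model with random intercepts for subject, for assigned table (the persistent effect) and for table-session (the weekly effect, which handles substitution). Use Satterthwaite or Kenward-Roger degrees of freedom. Add the same table terms to the repeated-measures ANCOVA.
3. **Fallback, stated in advance.** If there are too few tables to estimate the table variance, compare table means between arms.
4. **MMSE, CSDD and ZBI.** Add a random intercept for assigned table, at least as a sensitivity analysis.

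The cost is one log field and some analysis wording, plus fewer degrees of freedom and somewhat wider intervals. For the comparison of table means, four or five tables per arm leave 4 + 4 − 2 = 6 or 5 + 5 − 2 = 8 degrees of freedom, against 15 + 15 − 2 = 28 for the t test on subjects. The two-sided 5% critical value rises from 2.05 to 2.45 or 2.31, a factor of about 1.19 or 1.13.
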